## Abstract

**Background:**

Advanced primary care models emphasize patient-centered care, including self-management support (SMS), but the effective use of SMS for patients with type 2 diabetes (T2DM) remains a challenge. Interactive behavior-change technology (IBCT) can facilitate the adoption of SMS interventions. To meet the need for effective SMS intervention, we have developed Connection to Health (CTH), a comprehensive, evidence-based SMS program that enhances interactions between primary care clinicians and patients to resolve self-management problems and improve outcomes. Uptake and maintenance of programs such as CTH in primary care have been limited by the inability of practices to adapt and implement program components into their culture, patient flow, and work processes. Practice facilitation has been shown to be effective in helping practices make the changes required for optimal program implementation. The proposed research is designed to promote the translation of SMS into primary care practices for patients with T2DM by combining two promising lines of research, specifically, (a) testing the effectiveness of CTH in diverse primary-care practices, and (b) evaluating the impact of practice facilitation to enhance implementation of the intervention.

**Methods:**

A three-arm, cluster-randomized trial will evaluate three discrete strategies for implementing SMS for patients with T2DM in diverse primary care practices. Practices will be randomly assigned to receive and implement the CTH program, the CTH program plus practice facilitation, or a SMS academic detailing educational intervention. Through this design, we will compare the effectiveness, adoption and implementation of these three SMS practice implementation strategies. Primary effectiveness outcomes including lab values and evidence of SMS will be abstracted from medical records covering baseline through 18 months post-baseline. Data from CTH assessments and action plans completed by patients enrolled in CTH will be used to evaluate practice implementation of CTH and the impact of CTH participation. Qualitative data including field notes from encounters with the practices and interviews of practice personnel will be analyzed to assess practice implementation of SMS.

**Discussion:**

This study will provide important information on the implementation of SMS in primary care, the effectiveness of an IBCT tool such as CTH, and the use of practice facilitation to assist implementation.

**Trial registration:**

Registered with ClinicalTrials.gov – ClinicalTrials.gov ID: NCT01945918, date 08/27/2013. Modifications have been updated.

## Background

Most patients with type 2 diabetes mellitus (T2DM) in the U.S. receive diabetes care in primary care settings, which are undergoing rapid transformations due to the need to improve quality and decrease costs. The Patient Centered Medical Home (PCMH) and the Chronic Care Model (CCM) are complementary clinical intervention frameworks that are commonly employed to support better T2DM outcomes in primary care [1–7]. Self-management Support (SMS) is a core component of both the PCMH and CCM, and focuses on the central role of patients in managing their illness by engaging with and adopting healthy behaviors that promote optimal clinical outcomes [6, 8–10]. SMS typically targets improvements in medication adherence, diet, exercise, and other risk-related behaviors; all of which are crucial for maintaining good glycemic control and reducing the risks of diabetes-related complications. Despite its recognized importance, SMS programs for diabetes continue to demonstrate limited effectiveness and sustainability in the real world of primary care [11, 12]. Primary-care physicians have been unable to comprehensively and consistently address diabetes self-management within an efficient and systematic SMS framework for several interrelated reasons: they are often overwhelmed by competing demands, poorly trained in assessing and intervening with health behavior change, lack practice systems for implementing change and quality improvement, and receive inadequate reimbursement for time spent in SMS activities [13–16].

Few tools are available to assist practices with self-management support. Interactive behavior-change technology (IBCT) can facilitate the adoption of crucial SMS interventions in primary care for patients with diabetes and related health risk behaviors [17–20]. Compared with traditional, unstructured programs, technological options for delivery have the advantage of increased convenience and accessibility, and may provide individualized support and resources necessary for initiating and maintaining healthful lifestyles, especially when they include non-automated options to address patient preference and permit patient tailoring [19–22] There is strong evidence that Internet-based programs can effectively promote health behaviors to support diabetes self-management, [23] such as healthful eating/weight management, [24–27] increasing physical activity, [28–30] reducing depression symptoms, and smoking cessation [31, 32]. Multiple randomized trials have been conducted using IBCT programs for diabetes self-management with positive results [33, 34]. However, most current IBCT self-management programs contain several limitations to translation into primary care settings: [35, 36] they are largely informational, they require high literacy, they are limited to simple health-risk assessment without goal setting, action planning or follow-up, they fail to provide physician decision support, and they do not emphasize patient-physician collaboration. Furthermore, most are exclusively automated and do not take into account the preference of many patients and clinicians for different modes of assessment and intervention.

Connection to Health (CTH) is a comprehensive, evidence-based SMS program that supports behavior change through IBCT. The CTH logic model is informed by social-cognitive [37–39] and social-ecological [40–42] theories and is inclusive of the evidence based principles for implementing SMS in primary care [43]. Multiple intervention components work together to promote enhanced, tailored diabetes management, which is linked to positive health outcomes [44–46]. Patients complete a CTH assessment that covers multiple issues related to diabetes and co-morbid conditions using state-of-the-art measures, each with cut-points defining a flagged area for concern. Patients receive an immediate summary, along with profiles from prior assessments to denote change over time. Patients are asked to review the summary and identify areas to discuss with their care team in preparation for making an action plan. A parallel report is prepared for the clinician that also includes decision support tools and options for the clinician for each flagged area on the profile, all to assist in beginning a conversation with the patient about specific problems and how they might be addressed. Action planning plays a central role, and includes goal setting and problem solving [47] through an automated, web-based action planning program. CTH also includes patient resources and tips to improve diabetes management. CTH is avehicle for structuring and guiding a time-effective clinical conversation between patient and the care team, enabling clinicians and patients to regularly assess, monitor, and intervene with self-management issues using a patient-centered approach that allows for practice and patient tailoring and encourages patient/care team interaction.

The simple availability of effective IBCT tools like CTH does not assure their successful implementation [15, 16, 48–50]. Primary care practices are experiencing multiple pressures to see a large number of patients, to provide improved care, and to do so with very constrained reimbursement. Practices have few mechanisms to integrate new programs into routine care, which can exert major pressures on practice operations – even small changes can have substantial consequences that limit their effectiveness and sustainability [15, 16, 48–50]. Adoption and implementation of new care programs varies across practices based on practice characteristics, including practice culture and change capacity, practice size, location (rural vs. urban), previous change experience, and decision-making style [13, 14, 51].

Practice facilitation has been effective in assisting practices in implementing organizational changes such the CCM and PCMH [52–58]. A facilitator can assist a practice in tailoring a new program to fit their unique practice situation, resources, and culture, improving its implementation and its sustainability over time. Practice facilitators use a motivational interviewing approach in assessing and increasing key stakeholders’ motivation for change. The practice facilitation intervention impacts the practice’s capacity for change through forming a quality improvement team, [59] training the team in quality improvement techniques including the use of Plan-Do-Study-Act (PDSA) for rapid cycle change, planning and implementing work flow and other changes, and identifying and working to overcome barriers. The quality improvement team consists of a diverse group of representatives from the various clinician and staff roles in the practice and meets regularly to plan the adoption and implementation of programs like CTH.

This study has been designed to promote the translation of SMS into primary care practices for patients with T2DM by combining two promising lines of research; specifically, testing the effectiveness of CTH for patients with T2DM in diverse primary care practices and evaluating the impact of practice facilitation to enhance uptake and maintenance of the intervention. Our specific aims for this project are:

1. To conduct a cluster randomized trial to examine the reach, effectiveness, adoption, implementation, and maintenance (RE-AIM) of CTH for patients with T2DM in primary care practices.

2. To determine the incremental benefit of brief targeted practice facilitation on the implementation of CTH in diverse primary care practices.

3. To identify key practice characteristics (e.g., practice size, organization, setting, and level of experience with practice redesign efforts) that affect CTH RE-AIM outcomes.

## Methods

### Design

To address these aims, we will undertake a three-arm, *cluster-randomized trial* to evaluate the reach, effectiveness, adoption, implementation, and maintenance of CTH for patients with T2DM in diverse primary care practices (Fig. 1). Primary care practices will be randomly assigned to receive and implement the CTH program (CTH), the CTH program plus practice facilitation (CTH + F), or an SMS academic detailing educational intervention (SMS-Ed). Through this design, we will compare the effectiveness, adoption and implementation of these three SMS practice implementation strategies. To assure maximum generalizability, we will recruit a diverse group of practices in Colorado and California. We have chosen this design in order to examine the incremental effect of both CTH (CTH vs. SMS-Ed) and practice facilitation (CTH vs. CTH + F) on SMS outcomes, compared to an academic detailing educational intervention. Blinding of practice participants or study team is not possible.

**Fig. 1 Fig1:**
[figure not shown]
Timing of Enrollment, Interventions, and Assessments

### Interventions (see Table 1 and Fig. 1)

#### SMS education (SMS-Ed) arm

The SMS-ED arm serves as an attention control. Project staff will meet onsite with practice clinicians and staff members for two one-hour sessions to discuss what SMS is, why it is important, how primary care plays a role in this process, how others have approached it, and how it can be time and cost efficient for them to engage in SMS as part of standard diabetes care. Practices will have access to a website displaying general and local SMS resources, but will not have access to the formal CTH program. During this session, discussion of the implementation of these resources into the practice will be facilitated. No input will be provided regarding how unique practice characteristics might be utilized for more effective implementation of SMS, and CTH will not be introduced. Practices will be left to utilize these resources and to expand SMS activities as they see fit, without any further study input.

**Table 1 Tab1:** Program Elements across Project Arms

Program Element	SMS-Ed	CTH	CTH + F
Connection to Health computerized intervention program	No	Yes	Yes
Technical assistance with CTH implementation	No	Yes	Yes
Basic instructions on use of CTH	No	Yes	Yes
Assessment of baseline SMS and diabetes care activities	Yes	Yes	Yes
Feedback of assessment and recommendations for practice	No	No	Yes
Generic SMS education	Yes	Yes	Yes
Generic website with SMS resources	Yes	Yes	Yes
Practice facilitation: • Improvement team meetings – 4 over approximately 3 mos. • Workflow revision to implement CTH • Email contacts, other assistance between improvement team meetings and after 3 months as needed • Ongoing feedback of data regarding CTH usage	No	No	Yes

#### Connection to Health (CTH) arm

Practices in this arm will receive instruction in the use of the full CTH program, including web-based resources, but will not receive any practice facilitation to assist with adoption and implementation. The number and length of visits to these practices will be the same as for the SMS Education Arm, plus an additional one-hour training session on the technical aspects of CTH. The content of the visits will center on the use of CTH as a way to implement SMS. Clinicians and selected staff members will be given hands-on experience using the system and will be provided with scenarios that will highlight the effective use of CTH as a tool for diabetes SMS. The practices will then implement CTH on their own, with additional technical assistance provided as needed.

#### Connection to Health plus facilitation (CTH + F) arm

This arm includes the same three one-hour training sessions as CTH, but adds short-term, focused practice facilitation. The active practice facilitation phase includes four meetings of the practice improvement team, scheduled for approximately 60 min each. The improvement team will consist of diverse representatives (generally 6–10) of the practice. The facilitator will assist the team in developing a CTH adoption plan and then help them identify small goals for rapid cycle change using the Plan-Do-Study-Act QI model. Active facilitation will last for approximately 3 months, followed by monthly calls by the facilitator to review data regarding the practice’s use of CTH. A brief “booster” facilitation can also be scheduled to address subsequent problems.

### Patient samples

#### Patient population perspective

Since allocation of patients occurs at the level of the practice in this trial, all *patients* within a practice will be assigned to the same treatment condition, regardless of the extent to which the individual patient uses the tools provided. Although the intervention can potentially impact the entire population of patients with T2DM, each practice in the CTH and CTH + F arms will selectively utilize CTH with patients, and some patients introduced to CTH in a practice will follow through with it while others will not. Therefore, practices in each of the two arms with CTH will have patients who were and were not exposed to CTH. To preserve intent-to-treat approaches and alleviate potential selection bias at the level of individual patient recruitment, [66–69] we will evaluate the effect of CTH by defining two overlapping patient samples in each practice. The first will be a random sample of all patients with type 2 diabetes mellitus, ages 21 and over diagnosed for a minimum of 12 months, whether or not they participated in CTH – the “Evaluation Sample.” This sample will enable us to examine the effectiveness of the intervention on the primary outcome variables in the intent-to-treat analyses. A second sample in each practice will be comprised of only those patients with diabetes who complete the CTH assessment – the “CTH Sample.” This sample will be used in “as treated” (per protocol) analyses. It should be noted that these two samples are not independent of each other; e.g., many in the CTH sample will be included randomly in the Evaluation Sample. Each sample, however, will be utilized to address different research questions.

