#### Evaluation sample

Medical record reviews will be conducted on a random sample of patient who had received care in each practice for at least 1 year at baseline. Reviews will be conducted by research staff separate from the intervention team. The evaluator will be provided with a manual containing detailed instructions and will keep an audit log. A four-part data quality monitoring procedure will be employed consisting of use of a standardized abstraction protocol, extensive training in data abstraction, monitoring of Kappa values between the abstractors, and continuous quality improvement including periodic feedback to abstractors [70].

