### RE-AIM evaluation

We will use the RE-AIM framework to guide our evaluation [71–77].

***Reach*** will be assessed by comparing the percentage of eligible T2DM patients for whom there is evidence on chart review that SMS was provided by the practice across the three arms. The reach of the use of CTH will be assessed in two ways in the CTH and CTH + F practices: (1) the percent of eligible T2DM patients with whom CTH is used by the practice (number of eligible T2DM patients enrolled in CTH / total number of eligible T2DM patients with diabetes in the practice), and (2) comparisons of patients who use CTH vs. patients who do not participate in CTH on the basis of key demographic and medical history information.

***Effectiveness*** will be measured in intent-to-treat analyses by several sets of outcome variables collected from the evaluation sample by medical record review. Additionally, evaluation of patient-level “as treated” effects of participation in CTH will be carried out by comparing outcomes for patients enrolled in CTH to those not enrolled on all measures common to CTH.

***Adoption*** will be assessed by the participation and representativeness of practices recruited for the study.

***Implementation*** will be assessed by (a) the extent to which various intervention components are delivered to participants compared to intervention protocol; (b) description of practice-specific modifications to the basic protocol that seem to be effective; and (c) CTH website usage data.

**Maintenance** of the CTH system will be assessed by the extent of continued patient use of the CTH system over the intervention period, as well as the percent of practices at the 18-month follow-up continue using the CTH program.

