### Measures

#### Primary Effectiveness Outcomes

Will be obtained from the evaluation sample. HbA1c, LDL, systolic and diastolic blood pressure, and BMI will be abstracted from medical record reviews covering baseline through 18 months post-baseline. For each, the last measure prior to baseline will be used as the baseline measure.

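### The as-treated comparison groups patients by an undated event after baseline, so chart values from before a patient's first use of CTH can be classed as CTH outcomes

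*Protocol article*

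**What the plan says.** The Protocol article, under Patient population perspective, sets up two overlapping samples per practice. The Evaluation Sample is random and serves the intent-to-treat analyses. For the as-treated analyses, "A second sample in each practice will be comprised of only those patients with diabetes who complete the CTH assessment". No time limit or start date is given.

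Under RE-AIM evaluation (Effectiveness), the as-treated effect is to be estimated by "comparing outcomes for patients enrolled in CTH to those not enrolled on all measures common to CTH". This is a fixed two-group label.

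Under Primary Effectiveness Outcomes, HbA1c, LDL, blood pressure and BMI "will be abstracted from medical record reviews covering baseline through 18 months post-baseline", and "For each, the last measure prior to baseline will be used as the baseline measure". That section is written for the Evaluation Sample, but no other chart window or baseline rule appears in the article. The Evaluation sample section describes "a random sample of patient who had received care in each practice for at least 1 year at baseline", so baseline there is a study date for the practice, not the day a patient first used CTH.

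RE-AIM evaluation also plans to follow "the extent of continued patient use of the CTH system over the intervention period".

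**The concern.** Exposure to CTH starts when a patient first uses it, and that can be well after study baseline. Practices in the CTH arm put the program in place on their own. CTH + F practices first draw up an adoption plan during about three months of active facilitation. A patient first assessed at month 15 would, under a fixed label and an outcome window that opens at study baseline, bring 15 months of pre-CTH values into the CTH group.

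Two things follow. Pre-exposure values by themselves pull a true participation effect toward zero. The label is also set by later behaviour: a patient has to remain in the practice long enough to be assessed, and non-users meet no such condition. That second effect can push the estimate either way, so the net direction is unknown. Adjusting for baseline covariates does not correct a misdated exposure. At stake is whether the as-treated estimate can be read as an effect of taking part in CTH.

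**Working it through.** **The plan's own figure.** The article gives no figure for the as-treated analysis. Its stated power, under Power and sample size, belongs to the intent-to-treat comparison and reproduces:

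- Design effect: 1 + (30 − 1) × 0.01 = 1.29. Effective n per arm: 360 / 1.29 = 279.1.
- Power for 0.25 SD at two-sided alpha 0.05: 84.0% by normal approximation, 80.6% by a cluster-level t test with 22 df, and 81.8% with 33 df. All agree with the stated figure of more than 80%.
- 0.25 × 1.7 = 0.425, stated as 0.43 for HbA1c.

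The present point changes none of these.

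**Which data the contrast must use.** Patients who are not enrolled have no CTH assessments, so a comparison of enrolled with non-enrolled patients has to rest on chart data. The CTH sample section puts the combined chart reviews at up to 1800. The Evaluation Sample accounts for 30 × 36 = 1080, which leaves up to 1800 − 1080 = 720 further reviews. The only chart window and baseline value stated are those anchored at study baseline.

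**Illustrative size.** The article gives neither the distribution of first CTH use nor a measurement schedule for chart values. *Assumption:* first use is uniform over months 0 to T.

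*Quarterly values averaged over follow-up.* The share of values at month t that precede first use is max(0, 1 − t/T). Averaged over t = 3, 6, 9, 12, 15, 18:

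- T = 6: 0.50 / 6 = 8.3%
- T = 12: (0.75 + 0.50 + 0.25) / 6 = 25%
- T = 18: (0.833 + 0.667 + 0.500 + 0.333 + 0.167 + 0) / 6 = 41.7%

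If the effect is present only after first use, a true HbA1c difference of 0.425 would appear as 0.425 × (1 − share) = 0.39, 0.32 and 0.25 respectively.

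*Continuous follow-up instead of quarterly values.* The share is (T/2)/18 = T/36, which gives 17%, 33% and 50% for T = 6, 12 and 18. The apparent differences are 0.35, 0.28 and 0.21.

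*Only the last value, assumed uniform over months 12 to 18.* For T = 6 or 12 every patient has started before month 12, so the share is 0%. For T = 18, a third of first uses fall in months 12 to 18, and half of those come after the last value: 1/3 × 1/2 = 16.7%.

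These shares describe dilution only. They do not measure the bias from a label set by later behaviour.

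**The case against.** The strongest reply is that this is silence, not error. No sentence says that CTH patients count as treated from practice baseline, or that pre-CTH values enter the comparison as treated values. The window and baseline rule are written for the Evaluation Sample. Index dates and time-varying coding are commonly left to a SAP, and only a condensed article is at hand. This stands against any claim that misclassification is certain. It does not remove the point, because the article does fix a grouping by an undated event and a fixed contrast, and the only chart clock it supplies starts at study baseline. Put together, these allow the misclassification.

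The reply also narrows the scope. Under Secondary effectiveness outcomes from the CTH assessment, change is taken between a patient's own assessments, so those outcomes already start at first use. The power section speaks of a final HbA1c difference. If only a value at month 18 were used, the uniform model gives no pre-exposure values for uptake over 6, 12 or 18 months. Both limits stand.

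Three further readings are tempting and not well supported:

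- A reader might infer that enrolled and assessment-completed are two conflicting thresholds. The CTH sample section joins the terms, and no patient who enrols without completing the assessment is described. The difference in wording is minor.
- A reader might fault a dose-response claim. The article plans no such analysis.
- A reader might call this a full immortal-time problem. The outcomes are laboratory values, blood pressure and BMI rather than time to an event, and much of the retention issue is selection into CTH, which is a separate matter.

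**Conclusion.** The point holds for the as-treated chart comparison and nowhere else. As written, that comparison permits values from before first CTH use to be classed as CTH outcomes and labels patients by later behaviour. A reader might go further and conclude that the plan does credit all follow-up from practice baseline to CTH. The article does not say so.

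The size cannot be fixed from the article. Under assumed uniform first use, it runs from about 8% to 42% of quarterly values averaged over follow-up, and from about 0 to 17% if only the last value in months 12 to 18 is used. The 42% should not be quoted alone, because it needs both the slowest uptake considered and averaging over follow-up. The randomised comparisons, the power calculation and the repeat-assessment outcomes are untouched. The as-treated estimate should not be read as a participation effect until exposure is dated.

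**What to change.** In the as-treated chart analysis, take the date of the first completed CTH assessment as the start of exposure and model exposure as time-varying, so that earlier values count as unexposed. The longitudinal mixed models under Quantitative data analysis are stated for the intent-to-treat analyses, but the same model class can carry this term.

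Keep the common study-baseline value as the covariate for all patients. Re-anchoring only the users at their last value before CTH would give users and non-users baselines at different times and invite regression to the mean. If users are re-anchored, give non-users matched index dates in a landmark analysis.

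Use one exposure definition throughout, and leave the intent-to-treat analysis as it is.

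The cost is plan wording, a linkage of CTH dates to chart data, fewer exposed values for late users, and a slightly more complex model. Because identifying information stays in the practice, the linkage has to be done on site. With data collection complete, the sponsor should confirm that the dates are recorded and can still be linked. Selection into CTH is not solved by this change, and the estimate remains observational.
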